## 2. Materials and Methods

### 2.1. Setting and Design

This project will be carried out in the Psychiatry Departments of four hospitals in the Community of Madrid associated with the Instituto de Investigación Sanitaria Fundación Jiménez Díaz: Hospital Universitario Fundación Jiménez Díaz, Hospital Rey Juan Carlos, Hospital General de Villalba, and Hospital Infanta Elena. This protocol combines three complementary methodological perspectives: (1) a validation study; (2) an observational study; and (3) a single-arm pre-post study to evaluate the intervention. All patients identified with poor adherence will receive the same psychoeducational program; the pre-intervention measurement will serve as a comparator.

Figure 1 shows the outline of the project.

This protocol describes a study with three design perspectives to achieve our objectives:Validation study to explore the accuracy of digital self-report questionnaires.Observational study for identifying factors associated with non-adherence.Pre-post study to assess the effectiveness of the intervention

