### 2.3. Sample Size Calculation

According to our preliminary data, there are 5458 patients in our hospitals diagnosed with schizophrenia or bipolar disorder and with active antipsychotic dispensing registered in the MUP. Of these, an estimated 90% are registered on the Patient Portal, yielding an initial estimated sample of 4900 people.

Considering that completion of self-administered questionnaires on the Patient Portal is estimated to be around 30%, we expect an approximate sample of 1640 patients to perform the validation calculations for the adherence scales.

The sample size was calculated using G*Power (v3.1) for a one-sample means test (alpha = 0.05, power = 95%, effect size d = 0.5), yielding a minimum of 52 participants. This was based on previous studies exploring the ability of educational interventions to improve medication adherence in the medium term (Loots et al., 2021). Accounting for an anticipated dropout rate of up to 50%, the adjusted minimum is 104. We therefore set a recruitment target of 110 participants, well within the estimated pool of 656 patients expected to present with poor adherence.

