### 2.4. Procedure and Intervention

Project is expected to start in September 2026. We will access the MUP database and cross-reference it with data from the Patient Portal to identify our target sample, that is, those patients who received antipsychotic dispensations who also appear as active users of the Patient Portal. Within the entire sample, we will identify factors associated with adherence issues in the six months prior to the study. The entire sample will then be invited via a message through the Patient Portal to complete the self-report adherence questionnaires.

Finally, the subset of the sample identified with adherence problems will be the target sample for the intervention. Adherence problems to antipsychotics in people with schizophrenia or bipolar disorder are around 40–50%, although the variability in the studies is considerably high (Lingam & Scott, 2002). From the identified pool of patients with poor adherence, a recruitment target of 110 participants has been established. This sample size was determined using G*Power (v3.1) for a one-sample means test (alpha = 0.05, power = 95%, effect size d = 0.5), which requires a minimum of 52 participants (Loots et al., 2021). The final target of 110 accounts for an anticipated dropout rate of up to 50%, ensuring sufficient statistical power despite the high attrition typically observed in this clinical population.

The intervention program will be designed by clinical psychologists with experience in treating patients with bipolar disorder and schizophrenia after a review of the best protocols available in the literature. Presumably, participants will receive psychoeducational materials on the importance of adherence and the potential for mishap management. Tablet handling tips and medication-taking schedules will be reviewed. Participants will also be invited to a telehealth intervention comprising 10 online group psychotherapy sessions delivered via videoconference. These sessions will include cognitive-behavioral measures to manage adherence problems, and adherence will be monitored. Psychotherapy sessions will be led by clinical psychologists, and two sessions will feature testimonials from stabilized patients (See Figure 2).

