### 2.8. Statistical Analysis

Statistical analyses will be performed using R software version 4.5.3 and SPSS software version 30.0, or the latest versions available. All tests will be two-tailed, with 95% confidence intervals, and the level of statistical significance will be set at a *p*-value less than 0.05. The Morisky and Haynes scales (Morisky et al., 1986) will be measured prior to the intervention and again at the end of the sessions, and changes will be analyzed using Pearson’s correlation and simple regression. On the other hand, we will compare the total duration of antipsychotic exposure in the 6 months prior to the intervention with that in the 6 months following the intervention. Similarly, we will compare the average doses to which the sample was exposed before and after the intervention by calculating the recommended daily doses received.

To validate self-report questionnaires, sensitivity, specificity, positive predictive value, and negative predictive value will be calculated using medication collection data from the MUP as the gold standard. ROC curves will be constructed to determine the empirically optimal cut-off for classifying adherence, using the Youden index and reported with 95% confidence intervals, with PRE2DUP-derived antipsychotic exposure as the reference standard.

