To explore factors associated with higher or lower adherence, a logistic regression will be conducted, with adherence as the dependent variable. Adherence will be operationalized using the PRE2DUP method (Tanskanen et al., 2015; Taipale et al., 2016), generating two continuous outcomes: total duration of antipsychotic exposure (days) and average daily dose in DDDs (Tanskanen et al., 2015). These continuous variables will be used as dependent variables in all regression analyses. Furthermore, linear correlations will be performed between adherence levels (using percentage of adherence as a continuous variable) and various potentially implicated factors. To identify factors independently associated with non-adherence, a multivariable logistic regression model will be constructed, incorporating sociodemographic and clinical variables as independent predictors and adjusting for potential confounders (age, sex, diagnosis, comorbidities, and urbanicity). Simple logistic regression and Pearson correlations will be conducted as preliminary exploratory analyses to inform variable selection for the multivariable model. Pre-post changes in adherence outcomes—including PRE2DUP-derived exposure duration and average daily dose in DDDs, as well as self-report scale scores—will be analyzed using linear mixed-effects models, with time (pre- vs. post-intervention) as a fixed effect and subject as a random effect, adjusting for diagnosis, age, and sex.

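### The programme is delivered in therapy groups, but the pre-post model and the sample size treat participants as independent; if changes correlate within groups, the interval is too narrow and 95% power is not assured

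*Protocol article*

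**What the plan says.** Section 2.1 describes this part of the project as "a single-arm pre-post study to evaluate the intervention". Section 2.4 invites participants to "a telehealth intervention comprising 10 online group psychotherapy sessions delivered via videoconference". Clinical psychologists lead the sessions, and stabilised patients give testimonials in two of them. The article does not give the group size, the number of groups or the number of psychologists.

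Section 2.8 analyses pre-post change with a linear mixed model "with time (pre- vs. post-intervention) as a fixed effect and subject as a random effect", adjusted for diagnosis, age and sex. Subject is the only random effect.

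Section 2.3 sizes the comparison with a "one-sample means test (alpha = 0.05, power = 95%, effect size d = 0.5), yielding a minimum of 52 participants". It continues: "Accounting for an anticipated dropout rate of up to 50%, the adjusted minimum is 104". The target is then set at 110. Neither 2.3 nor the repeat of the calculation in 2.4 mentions a group size, an ICC or a design effect. The limitations in 4.3 do not mention clustering.

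**The concern.** People in one therapy group share a psychologist, the discussion and up to ten sessions, so their changes in adherence may resemble each other. A subject random effect handles the two measurements on one person. It does nothing for correlation of changes between people in the same group.

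In a single-arm study the mean change is the whole effect estimate. Any between-group variance in change therefore goes straight into its standard error, and a model without a group term leaves that variance out. The interval is then too narrow and the p-value too small. A larger sample does not cure this if the groups stay the same size.

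The article itself fixes the random-effects structure and the sample size calculation, so these are not details left to an analysis plan. The effectiveness result is also meant to inform wider use of the programme (4.2 and 5).

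**Working it through.** **Inputs from the article.** One-sample test, alpha 0.05, power 95%, d = 0.5 and n = 52 (2.3); two-sided testing, "All tests will be two-tailed, with 95% confidence intervals" (2.8); dropout up to 50%, adjusted minimum 104, target 110 (2.3).

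**Assumed, because the article does not give them.** Analysed group size m = 5 or 10; ICC of change 0.01 to 0.10; equal groups. The two sizes are linked: groups of 10 that lose half their members leave 5 analysed.

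**Reproducing the plan.** n = ((1.960 + 1.645)/0.5)² = 51.98, so 52; and 52/(1 − 0.5) = 104. Both match, with participants independent (design effect 1). The exact two-sided t-test at 52 has power 94.3% and needs 54 for 95%, so the stated 95% at 52 is the normal approximation.

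**Adding groups.** Design effect DE = 1 + (m − 1) × ICC.
- Type I error when groups are ignored: 2 × [1 − Φ(1.96/√DE)].
- Power at 52 from the design effect alone: t-test with 51 degrees of freedom and noncentrality 0.5 × √(52/DE).

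| ICC | DE, m = 5 | Type I, m = 5 | DE, m = 10 | Type I, m = 10 | Power at 52, m = 5 |
|---|---|---|---|---|---|
| 0 | 1.00 | 5.0% | 1.00 | 5.0% | 94.3% |
| 0.01 | 1.04 | 5.5% | 1.09 | 6.0% | 93.4% |
| 0.02 | 1.08 | 5.9% | 1.18 | 7.1% | 92.6% |
| 0.05 | 1.20 | 7.4% | 1.45 | 10.4% | 89.8% |
| 0.10 | 1.40 | 9.8% | 1.90 | 15.5% | 84.8% |

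A simulation with 110 participants in groups of 10 (20,000 replicates) gave type I errors of 5.9%, 7.2%, 10.5% and 15.3% for the four positive ICCs, in line with the formula. The standard error is understated by 1 − 1/√DE: 1.9% to 15.5% with groups of 5, and 4.2% to 27.5% with groups of 10.

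**Two separate costs.** A t-test on 10 group means (50 participants, 9 degrees of freedom) has power of about 88% even at ICC 0. Simulated power of a group-means test at about 52 in groups of 5 was 87%, 86%, 83% and 77% for the four positive ICCs. Most of the gap from 95% at small ICC is therefore the price of few degrees of freedom and not the effect of correlation. The last column of the table isolates the correlation.

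**Margin at the target.** With the full 50% dropout, 110 leaves 55 analysed. The tolerable design effect for 95% power (normal approximation) is 55/51.98 = 1.06. At 40% dropout it is 66/51.98 = 1.27, and at 30% it is 77/51.98 = 1.48. With 66 analysed in groups of 5 and ICC 0.10 (DE 1.40), power is Φ(0.5 × √(66/1.40) − 1.96) = 93%. With all 110 analysed in groups of 10, even the group-means test has simulated power of 99.4%, 99.1%, 97.6% and 92.5%. Lower dropout does not protect every case: 66 analysed in groups still of 10 at ICC 0.10 gives 83.8%, and 77 gives 88.9%.

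**The case against.** The strongest reply is that the consequences depend on two quantities that the article does not give. At an ICC near zero, the model's standard error is right and the power is as planned. This stands. A reader might infer that the standard errors are certainly too small and that 95% power is certainly missed. The article does not support that.

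For power, three further points stand. The 50% dropout is a ceiling. Exposure comes from the prescription system, so a participant who leaves the sessions need not be lost for that outcome, although the self-report scales would be. With all 110 analysed in groups of 10, three of the four ICC scenarios exceed 95% power.

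It is also fair to say that the group structure is not yet settled. Section 2.4 describes a programme still to be designed, and participants are only invited. Those who attend no group share nothing, which dilutes the average correlation.

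None of this rescues the model as stated. Delivery in groups is fixed in 2.4, subject is the only random effect in 2.8, and no other section allows for correlated change.

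**Conclusion.** The point holds conditionally. The pre-post model and the sample size both assume independence between participants, which does not fit the stated mode of delivery. If changes correlate within groups, the interval is too narrow. Over the assumed ICCs of 0.01 to 0.10, the nominal 5% error becomes about 5.5% to 9.8% with groups of 5 and 6.0% to 15.5% with groups of 10.

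The validity of the interval matters more than the power. At 52 analysed in groups of 5, the loss due to correlation is about 1 to 9 percentage points (94.3% to between 93.4% and 84.8%). At 55 analysed there is almost no margin. With all 110 analysed, power stays at about 92% or more over this range, and so it does with 66 analysed in groups of 5 from the design effect alone.

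These figures assume equal groups with everyone attending. Non-attendance would make the problem smaller; larger groups would make it worse.

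**What to change.** - **Data collection:** record each participant's therapy group, and the psychologist who leads it.
- **Section 2.8:** base the pre-post inference on a cluster-robust interval with a small-sample correction, or on a therapy-group random effect on the change (a random time slope by group) with small-sample degrees of freedom. A group random intercept alone is not enough, because it cancels out of the pre-post difference. Treat participants who attend no group as singletons.
- **Section 2.3:** state that the 95% power assumes no within-group correlation, and give power for the planned group size over an ICC range. The recruitment target can stay as it is.

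The cost is one or two recorded variables and one change to the model. This is easy before the planned start in September 2026, whereas group membership may be hard to reconstruct later. The downsides are a somewhat wider interval, a less favourable stated power and, with few groups, a group variance that is estimated imprecisely and may come out at zero.

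### A pre-post mixed model with only a subject random effect can give intervals that are too narrow, and a biased change, for any outcome with many missing post values, chiefly the self-report scales

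*Protocol article*

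**What the plan says.** Section 2.8 (Statistical Analysis) gives the pre-post model as a linear mixed-effects model, "with time (pre- vs. post-intervention) as a fixed effect and subject as a random effect, adjusting for diagnosis, age, and sex". It covers several outcomes, "including PRE2DUP-derived exposure duration and average daily dose in DDDs, as well as self-report scale scores". No residual variance structure is given.

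Three design features bear on this model:

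- **Single arm.** In 2.1, "the pre-intervention measurement will serve as a comparator".
- **Selection.** In 2.4, "the subset of the sample identified with adherence problems will be the target sample for the intervention". The measure that defines an adherence problem for this purpose is not fixed.
- **Dropout.** In 2.3, "Accounting for an anticipated dropout rate of up to 50%, the adjusted minimum is 104".

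The outcomes come from two sources. Exposure and dose are read from the dispensing register (MUP; 2.5 and 2.8). The self-report scales are answered by the patient before the intervention and again when the sessions end (2.8).

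**The concern.** With two time points, one subject intercept and one residual variance, the fitted pre and post variances are equal by construction. Selecting people for low baseline values tends to shrink the pre variance and leave the post variance larger.

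With complete pairs this does not matter. When many post values are missing, two things go wrong. The post mean, which rests on fewer patients, is given a pooled variance that is too small. The model also predicts the missing post values from baseline with the wrong slope. The second fault causes bias when dropout depends on baseline, even though such data are missing at random, the situation in which a mixed model is normally trusted.

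At stake are the interval and p-value for the pre-post change (third objective in 1.5, first hypothesis in 1.6) on each outcome with substantial missing post data. The error discussed here is measured against the selected group's own true change, so it is distinct from regression to the mean.

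**Working it through.** **1. The plan's own figures.** The sample size is set "for a one-sample means test (alpha = 0.05, power = 95%, effect size d = 0.5), yielding a minimum of 52 participants", and 2.8 states "All tests will be two-tailed, with 95% confidence intervals". The normal approximation gives ((1.960 + 1.645)/0.5)² = 51.98, so 52; the exact t test gives 54. Allowing for dropout, 52/(1 − 0.50) = 104, and the target is 110. At 50% dropout, 110 pre values would stand beside about 55 post values. The pool of 656 is 656/1640 = 40% of the expected questionnaire completers, which is the source of the 40% selection fraction used below.

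**2. Assumptions.** The article gives no SDs, pre-post correlation or dropout mechanism. Assumed: normal scores with population SD 1, lowest 40% selected, pre-post correlation r = 0.3 to 0.7, n = 110, half the post values missing. Covariates are left out.

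**3. What selection does to the variances.** The cut-off is c = −0.253 and λ = φ(c)/0.40 = 0.966.

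- Pre variance: 1 − cλ − λ² = 1 + 0.245 − 0.933 = 0.312, so the SD is 0.56.
- Post variance: 1 − r²(1 − 0.312).

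| r | Post SD | Post/pre SD ratio |
|---|---|---|
| 0.3 | 0.97 | 1.73 |
| 0.5 | 0.91 | 1.63 |
| 0.7 | 0.81 | 1.46 |

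For a bounded 0 to 100% measure the ratio ranged from 0.94 to 1.70. It falls towards 1 when improvement reaches the ceiling.

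**4. Complete pairs.** The time effect is the mean paired difference. With pooled variance S = (V_pre + V_post)/2, the model variance is 2(S − Cov)/n = (V_pre + V_post − 2Cov)/n, which is the paired variance. Unequal variances do no harm. Simulated coverage was 94.3 to 95.5%.

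**5. Why missing post values break this.** Take r = 0.5. The covariance after selection is 0.5 × 0.312 = 0.156. The correct slope of post on pre is 0.156/0.312 = 0.50. With the variances pooled over pairs, the slope is 0.156/[(0.312 + 0.828)/2] = 0.27. The bias is approximately (model slope − true slope) × (baseline mean of all − baseline mean of completers). If low-baseline patients leave more, both factors are negative and the bias is upward. If high-baseline patients leave more, it is downward. If dropout is random, the second factor is zero on average and only the standard error is wrong.

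**6. Simulated size, selection on the analysed measure.**

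| Dropout (about 50%) | Random intercept: bias (population SD) | Random intercept: 95% interval misses | Unstructured: misses |
|---|---|---|---|
| Random | 0 | about 8–10% | about 5–6% |
| Moderately more among low baseline | +0.03 to +0.06 | about 11–12.5% | about 5–6% |

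With random dropout the model SE was 83, 87 and 89% of the true SE for r = 0.3, 0.5 and 0.7. One moderate-dropout case in detail (r = 0.5, logit slope 0.7 per baseline SD): the random intercept had bias +0.055, empirical SE 0.124, model SE 0.105 and 11.9% misses. The unstructured model had bias 0.001, SEs of 0.130 and 0.131, and 4.8% misses.

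The results depend on how strongly dropout follows baseline. In a second set of runs with larger biases, more dropout at low baseline gave +0.05 to +0.08 and 12 to 17% misses. More dropout at high baseline gave −0.03 to −0.06 and 11 to 15%. The unstructured model kept 94 to 96% coverage throughout.

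**7. When the effect is small or reversed.**

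- Selection on another measure correlated 0.5 with the outcome. For r = 0.5 the pre variance is 1 − 0.25 × 0.688 = 0.828. If the selection measure relates to the post value only through the pre value (correlation 0.25), the post variance is 1 − 0.0625 × 0.688 = 0.957. The SD ratio is then √(0.957/0.828) = 1.08. Misses were about 5 to 8%, and bias was at most 0.02.
- 20% dropout at random: 5.7% misses, against 4.8% for the unstructured model.
- Post SD smaller than pre (ratio 0.6), dropout at random: the interval is too wide (coverage 97.6%). If low-baseline patients leave more, the bias reverses to −0.10.

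**The case against.** The strongest reply is that the two harmful conditions, many missing post values and selection on the analysed measure, are not shown to meet in any one outcome. Exposure and dose come from pharmacy records, which are not lost when a patient stops attending video sessions, and 4.3 links expected dropout to telehealth attrition. The 50% is a participant dropout rate, not a stated rate of missing dispensing data. The scales can go missing, but if poor adherence is identified from dispensing, selection is not on the scales. This stands, and it limits the point. It does not remove it: 2.5 names the self-report scales for the main outcome (although 4.3 gives dispensing data as primary), the same model is applied to them, and the selection measure is left open.

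A second reply is that the article does not rule out time-specific residual variances, and that this detail often belongs in an analysis plan, which is not shown. It is true that the article never states equal variances. But it does name a concrete model, and that model in its ordinary form has a single residual variance.

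A third reply is that regression to the mean is larger. Under the same assumptions it is (1 − r) × 0.966 = 0.29 to 0.68 population SD. That is correct, and the fix proposed here leaves it untouched.

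**Conclusion.** The point holds in a conditional form, as a worthwhile improvement to the analysis. For an outcome with about half its post values missing and selection on that same outcome, the nominal 95% interval misses the true change about 8 to 12% of the time. Bias is about 0.03 to 0.06 population SD when dropout depends moderately on baseline. These figures rest on assumed normality, correlations of 0.3 to 0.7, selection of the lowest 40%, and dropout at the top of the anticipated range.

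A reader might infer that every pre-post interval in this study will be too narrow and the effect overstated. The documents do not support that. Intervals that are too narrow require a post SD above the pre SD, which is likely after selection but not given. Overstatement also requires the less adherent to leave more. Nor do the documents show that half the post values will be missing for dispensing-based exposure and dose. If those are complete, the six-month effectiveness comparison on them is unaffected.

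**What to change.** In 2.8, replace the single subject random effect with an unstructured 2x2 within-subject covariance: separate pre and post variances and a free correlation, fitted by REML with time as a fixed effect and the same covariates. Both named packages can fit it. State also that MUP exposure and dose will be obtained for participants who leave the sessions, as far as their consent allows, so that these pairs are as complete as possible.

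The analysis change costs one extra variance parameter and one sentence of text. Where the post variance is larger and values are missing, intervals become slightly wider; with complete pairs the answer is the same. The sample size does not change. Regression to the mean needs its own remedy.
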